### Ethical Clearance

All participants (chiropractors and patients' with spinal pain) will provide voluntary written informed consent with a full understanding of what study participation entails and the potential risks. Ethics approval has been obtained from Murdoch University's Human Research Ethics Committee (Reference number 2011/109).

### Demographic Material and Assessment of Outcomes

#### 1. Chiropractor Demographics and Usual Chiropractic Care Characteristics

For the participating chiropractors, the following demographic characteristics will be collected: age, years in practice, institution from which qualifications were obtained, and speciality certification or additional qualifications. A treatment checklist will be used to collect information about the types of treatments used in each usual chiropractic care appointment. Collection of the demographic and treatment information accords with the CONSORT Recommendations for the Reporting of Nonpharmacologic Trials [10]. Information about the types of treatment used will also be used for later analysis and correlation with adverse events.

#### 2. Baseline Assessment

The following questionnaires will be administered at baseline: demographic questionnaire; NRS [12]; FRI [13]; Fear-Avoidance Behaviour Questionnaire (FABQ) [19]; SF-36 [20]; STarT Back Musculoskeletal Screening Tool [21]; and the Pain Catstrophising Scale (PCS) [22]. Also, the primary area of concern for each participant will be identified and one of the following questionnaires specific to that area will be administered: the modified Oswestry Disability Index (ODI) [23]; or Neck Disability Index (NDI)[24].

Descriptive statistics from the baseline measures including the SF-36, STarT Back Musculoskeletal Screening Tool, and demographic questionnaire will be examined to determine if clinically important differences are evident between the usual chiropractic group and sham group at baseline. The SF-36 is a well validated and extensively used measure of general health status [25]. The STarT Back Musculoskeletal Screening Tool is brief validated instrument that has been developed to identify people with chronic pain who are more likely to experience persistent symptoms [21]. The demographic questionnaire enquires about age, sex, race/ethnicity, education, household income, marital status, employment status, smoking, and alcohol and legal drug consumption. These items were derived from classifications used by the Australian Bureau of Statistics [26].

A baseline symptom checklist will be administered to examine whether the adverse events that participants reported after each chiropractic treatment were actually an adverse event or the persistence of a presenting complaint. This will be achieved through comparing data from the symptom checklist taken at baseline to data from the adverse event checklist collected after each chiropractic treatment.

The NRS contains an 11-point scale varying from 0 (no pain) to 10 (worst pain imaginable) [12]. It is a valid, reliable and responsive measure of pain intensity [27]. Participants will be asked to use the scale to rate: their worst level of pain in the last two days; average pain level in the last two days; best pain level in the last two days; and current pain.

The FRI contains 10 questions which enquire about the impact of neck and back pain on physical function. It was designed to assess conditions where more than one area of the spine is involved and is valid, reliable and responsive [13].

The NDI was designed to measure neck-specific disability. The questionnaire has 10 items concerning pain and activities of daily living. It has demonstrated validity, reliability and responsiveness [24].

The modified ODI is a region-specific outcome measure that has been shown to have high levels of reliability, validity and responsiveness in patients with low back pain [23]. It assesses impact of low back pain on physical function and activities of daily living.

The FABQ will be used to assess participant's beliefs about the relationships between back pain, work, and physical activity. The FABQ has good test-retest reliability [19], and predictive validity for future episodes of LBP [23] and clinical outcome [15].

Catastrophising will be assessed with the PCS [22]. The PCS assesses different dimensions of negative thoughts related to pain: rumination, magnification, and helplessness. It contains 13 items scored on a 5-point Likert-type scale varying from 0 ("not at all") to 4 ("all the time"). The PCS has been shown to be a reliable and valid measure which predicts postoperative pain intensity following lumbar spine surgery [28].

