**Methods:**

One hundred and eighty participants will be randomly allocated to either usual chiropractic care or a sham intervention group. To be considered for inclusion the participants must have experienced non-specific spinal pain for at least one week. The study will be conducted at the clinics of registered chiropractors in Western Australia. Participants in each group will receive two treatments at intervals no less than one week. For the usual chiropractic care group, the selection of therapeutic techniques will be left to the chiropractors' discretion. For the sham intervention group, de-tuned ultrasound and de-tuned activator treatment will be applied by the chiropractors to the regions where spinal pain is experienced. Adverse events will be assessed two days after each appointment using a questionnaire developed for this study. The efficacy of short term chiropractic care for spinal pain will be examined at two week follow-up by assessing pain, physical function, minimum acceptable outcome, and satisfaction with care, with the use of the following outcome measures: Numerical Rating Scale, Functional Rating Index, Neck Disability Index, Minimum Acceptable Outcome Questionnaire, Oswestry Disability Index, and a global measure of treatment satisfaction. The statistician, outcome assessor, and participants will be blinded to treatment allocation.

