### Treatment allocation

When participants visit Murdoch University and after baseline measures and consent have been obtained, one of the research staff, excluding the research assistant (RA) and statistician, will randomly allocate the participants to one of the two groups using a 1:1 allocation. A statistician will generate a permuted block randomization sequence allocating persons to either chiropractic care or the sham group. The group assignment will be written on small cards and placed in opaque envelopes.

For ethical reasons, participants in the sham group will be offered two treatments of usual chiropractic care two weeks after receiving the last sham treatment and following receipt of their final outcome measures by the RA. Any participant who discontinues treatment will be followed-up to determine the reason for discontinuation.

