#### 3. Assessment of Adverse Event Events

To accord with the CONSORT extension for Better Reporting of Harms [11], it is necessary to *a priori *define anticipated and unanticipated adverse events and explicitly state these definitions in reporting the methods for this study. Anticipated adverse events for this study are defined as the adverse events listed in the questionnaire developed for this study and any of the other adverse events reported in the studies conducted by Senstad et al. [3], Hurwitz et al. [4], Rubinstein et al. [6], and Theil et al. [5]. Unanticipated adverse events will be defined as stroke, fracture, dislocation, or disc injury.

Information about adverse events will be collected after each chiropractic appointment. Participants will be asked to complete the questionnaire two days after each appointment as adverse events typically manifest within two days of chiropractic treatment [3,4,6].

The adverse events questionnaire [Additional file 1] was derived from a checklist used by Cagnie et al. [29]; open-ended questions from Senstad et al. [3] and Hurwitz et al. [4]; adverse events reported in RCT's [4,6,29-32]; and two surveys [5,33]. It consists of items which enquire about the onset and severity of adverse events, and items about the impact of adverse events on activities of daily living. We decided to use a questionnaire which consisted largely of predefined response options as previous studies have demonstrated that the use of predefined response options results in more comprehensive reporting of adverse events [34].

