#### Analysis of Adverse Events

The primary outcome (adverse event; yes/no) will be compared between groups. The severity and frequency of adverse events will be reported descriptively. Logistic regression will be used to examine associations between adverse events and several factors. Factors which have been significantly associated with adverse events in previous studies will be selected for this study. These factors comprise treatment satisfaction [4], manipulation/mobilisation [4], global improvement [4], GP visit in last six months [6], duration of neck/back pain [6], medication use [29], gender [29], and age [29]. The relative risk [39] will be calculated using a two by two contingency table and 95% confidence intervals. The number needed to harm [40] will be calculated with 95% confidence intervals to identify the number of individuals needed to be exposed to a risk factor (chiropractic treatment) over a specific period to cause harm (adverse outcome) in one patient that would not otherwise have been harmed. Data will be assessed by using per protocol analysis. In addition, an intention to treat analysis will be undertaken by using sequential regression multiple imputation [41].

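### Both adverse event forms are compared with one symptom checklist taken before randomisation, so the comparison alone cannot separate a reaction to treatment 2 from a lingering first reaction or a symptom that began between visits

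*Protocol article*

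**What the plan says.** All places are in the protocol article.

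- **Purpose of the checklist** (2. Baseline Assessment). It is there to decide whether symptoms reported after treatment "were actually an adverse event or the persistence of a presenting complaint".
- **Method** (same section). This is done by "comparing data from the symptom checklist taken at baseline to data from the adverse event checklist collected after each chiropractic treatment".
- **When it is taken** (Treatment allocation). Participants are allocated "after baseline measures and consent have been obtained", at the university visit. Treatment is given later, at the chiropractors' clinics.
- **Spacing of treatments** (Abstract, Methods). "Participants in each group will receive two treatments at intervals no less than one week". No maximum is stated.
- **When the forms are completed** (3. Assessment of Adverse Event Events). "Participants will be asked to complete the questionnaire two days after each appointment".
- **What the form asks** (same section). "It consists of items which enquire about the onset and severity of adverse events". The form is an additional file and is not shown.
- **Analysis** (Analysis of Adverse Events). "The primary outcome (adverse event; yes/no) will be compared between groups", and "The severity and frequency of adverse events will be reported descriptively".

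No symptom check between the two treatments is described, and no rule is given for assigning an event to treatment 1 or treatment 2.

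**The concern.** The stated comparison asks one question of each form: was this symptom present at baseline? For the second form that reference is out of date. Two kinds of symptom pass the test without being reactions to treatment 2:

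- a reaction to treatment 1 that has not yet resolved;
- a headache, tiredness or similar complaint that began for other reasons after baseline and before treatment 2.

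The protocol justifies its two-day form by saying that adverse events usually appear within two days of treatment. The baseline comparison instead covers the whole time since the university visit, so its window is wider than that rationale.

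Three uses of the data are exposed. The first is the frequency of events, which is part of aim 1 and is reported descriptively. The second is any count by treatment. The third is the later analysis, described under Chiropractor Demographics and Usual Chiropractic Care Characteristics, that correlates events with the techniques recorded at each usual-care appointment. There a carried-over reaction could be linked to the wrong appointment.

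**Working it through.** **1. Age of the reference.** The interval between treatments is at least 7 days and the form follows 2 days after an appointment. The second form is therefore completed at least 7 + 2 = 9 days after treatment 1. Its distance from baseline is longer by the gap between the university visit and treatment 1, which is not stated.

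**2. The plan's own figure.** Inputs from Sample Size: 45% v 25%, two-sided alpha 0.05, 90 per group. With the pooled z-test,

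power = Φ{ [ |p1 − p2|√n − 1.96√(2p̄(1 − p̄)) ] / √(p1(1 − p1) + p2(1 − p2)) }.

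Here p̄ = 0.35, so power = Φ{ (1.897 − 1.322) / 0.660 } = Φ(0.872) = 80.8%. The same method needs 89 per group for 80% power. The stated 90 per group and 80% are reproduced. The planned relative risk is 0.45/0.25 = 1.80 and the number needed to harm is 1/0.20 = 5.0.

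**3. Unrelated new symptoms.** Assume a share u of otherwise event-free participants, the same in both arms, gains a false yes. Each rate becomes p′ = p + (1 − p)u. The documents give no value for u, so 5% and 10% are illustrations.

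| u | Usual care | Sham | Relative risk | Number needed to harm | Power at 90 per group |
|---|---|---|---|---|---|
| 0 | 45.0% | 25.0% | 1.80 | 5.0 | 81% |
| 5% | 47.8% | 28.8% | 1.66 | 5.3 | 75% |
| 10% | 50.5% | 32.5% | 1.55 | 5.6 | 69% |

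For example, at u = 10%: 0.45 + 0.55 × 0.10 = 0.505; 0.25 + 0.75 × 0.10 = 0.325; 0.505/0.325 = 1.55.

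**4. Lingering first reactions.** Assume equal, independent visit rates q with 1 − (1 − q)² equal to the planning rate. Then q = 1 − √0.55 = 25.8% in usual care and 1 − √0.75 = 13.4% in sham. If a share L of first reactions is still reported on the second form, that form's rate becomes q + (1 − q)qL. With L = 20% (an assumption):

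- usual care: 0.258 + 0.742 × 0.258 × 0.20 = 29.7%, against 25.8%;
- sham: 0.134 + 0.866 × 0.134 × 0.20 = 15.7%, against 13.4%.

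The apparent excess at the second visit goes from 12.4 to 14.0 points. Carry-over is proportional to true reactions, so it is not equal between arms.

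**5. Effect on a per-patient outcome.** A participant with a lingering first reaction already scored yes on the first form. The share with any event stays at 45% and 25% whatever L is. Only the mechanism in step 3 can change that outcome.

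**The case against.** The strongest reply is that the documents never say how such symptoms are scored. A reader might infer that every lingering or unrelated symptom is counted as an event of treatment 2. No section states that rule, and the form asks about onset, which is the natural way to catch a symptom that began earlier. This stands: whether the onset items do the job cannot be judged without the form. What can be said is that the comparison in 2. Baseline Assessment makes no mention of onset.

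Second, the checklist was given the narrower task of recognising presenting complaints, and for that an untreated baseline is the right reference. Background symptoms are left to the sham arm, which Materials and methods includes partly to account for natural history. This stands in part. Background events equal in both arms create no spurious difference. They do stay in the absolute frequencies, and they dilute the relative risk.

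Third, a reader might take the power figures as proof that the trial is underpowered. They are not. The 45% is argued from a single-arm study, and the Background itself says uncontrolled studies may overstate event rates through natural history or placebo response. The 25% for sham is set well above the 7% mild event rate cited for the same de-tuned ultrasound method. Both rates may already contain background events, and adding u would then count them twice.

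Fourth, replacing baseline by a checklist before treatment 2 could hide harm. A delayed reaction to treatment 1 that starts after the first form and is present at the second visit would be missed by the first form and subtracted from the second. This objection is sound and shapes the fix.

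**Conclusion.** The point holds in a limited form. As described, the comparison with a single pre-randomisation checklist cannot by itself assign a symptom on the second form to treatment 2. Such symptoms may be scored there unless the onset items catch them.

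The firm consequences are for descriptive frequency, per-treatment counts and the correlation of events with techniques. The primary outcome reads as any event per patient, since Sample Size is framed as the share of patients with an event. On that reading a persisting first reaction does not change it.

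Unrelated new symptoms can add false positives in both arms. At an assumed 5% or 10% of otherwise event-free participants, the relative risk would be 1.66 or 1.55 instead of 1.80, and power 75% or 69% instead of 81%. These are upper views if the planning rates already include background. The sample size calculation itself is sound, and nothing here shows a bias that would create a difference between arms in the per-patient outcome.

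**What to change.** - Add the same short, self-completed symptom checklist immediately before each of the two treatments, in both arms.
- Use it together with the baseline checklist and the onset items to assign each event to a treatment, and state how the onset items are used.
- Count a reaction carried over from treatment 1 once, under treatment 1.
- Report any symptom absent at baseline but present before treatment 2 as a separate between-visit event. Do not discard it, so that delayed reactions to treatment 1 are not lost.
- Report the primary any-event comparison with and without these between-visit events.

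The cost is one short page at each of two visits already scheduled. The downsides are slightly more form-filling and some prompting of symptom reports, which should be equal in both arms. Unrelated symptoms that begin within the two days after a treatment would remain, and the sham comparison is suited to those.

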#### 3. Assessment of Adverse Event Events

To accord with the CONSORT extension for Better Reporting of Harms [11], it is necessary to *a priori *define anticipated and unanticipated adverse events and explicitly state these definitions in reporting the methods for this study. Anticipated adverse events for this study are defined as the adverse events listed in the questionnaire developed for this study and any of the other adverse events reported in the studies conducted by Senstad et al. [3], Hurwitz et al. [4], Rubinstein et al. [6], and Theil et al. [5]. Unanticipated adverse events will be defined as stroke, fracture, dislocation, or disc injury.

Information about adverse events will be collected after each chiropractic appointment. Participants will be asked to complete the questionnaire two days after each appointment as adverse events typically manifest within two days of chiropractic treatment [3,4,6].

The adverse events questionnaire [Additional file 1] was derived from a checklist used by Cagnie et al. [29]; open-ended questions from Senstad et al. [3] and Hurwitz et al. [4]; adverse events reported in RCT's [4,6,29-32]; and two surveys [5,33]. It consists of items which enquire about the onset and severity of adverse events, and items about the impact of adverse events on activities of daily living. We decided to use a questionnaire which consisted largely of predefined response options as previous studies have demonstrated that the use of predefined response options results in more comprehensive reporting of adverse events [34].

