### Withdrawing Participants from this Study

A stopping rule was defined for withdrawing participants from this study in accordance with recommendations in the CONSORT extension for Better Reporting of Harms [11]. If a participant reports to their chiropractor or research staff a severe adverse event they will be withdrawn from the study and referred to their local doctor or hospital emergency department depending on the nature of the event. Each participant will complete an adverse event questionnaire two days after each chiropractic appointment and asked to then return it in a reply paid envelope. Any adverse event will be classified as severe if it is thought to be an emergency situation e.g. stroke or the associated pain intensity is rated above 8/10 on an 11 point NRS, which accords with the definition for a serious adverse event by Rubinstein et al [6].

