#### 4. Assessment at Two Week Follow-Up

We will administer at two week follow-up the NRS [12], FRI [13], and the area specific instruments modified ODI [23] or NDI [24]. These questionnaires will be used to establish the short term efficacy of brief chiropractic care for spinal pain. The FABQ [19] and PCS [22] will also be administered to examine whether cognitive aspects related to the experience of pain influence pain severity, physical function and adverse events.

Also, a global measure of treatment satisfaction [27] and global measure of perceived change [35] will be administered at two week follow-up. The global measure of treatment satisfaction [27] will be used to examine the association between adverse events and treatment satisfaction. It will be measured on a five point categorical scale (very dissatisfied = 0; dissatisfied = 1; no preference = 2; satisfied = 3; very satisfied = 4). The global measure of perceived change [35] will be used to examine the association between adverse events and overall perceived change in the main complaint. It will be measured on an 11 point continuous scale varying from -5 to +5 (-5 = much worse, 0 = unchanged, +5 much better).

Blinding will be assessed at two weeks with a questionnaire [36] that asks the participants if they were in the real treatment group or the sham treatment group. The possible responses are: real treatment group; sham group; or don't know.

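### The unanticipated class of adverse events is a closed list of four foreseen diagnoses, and no adverse event question is scheduled later than two days after a treatment

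*Protocol article*

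**What the plan says.** All references are to the protocol article.

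- **Classes of event** (3. Assessment of Adverse Event Events). The section says that the harms-reporting guideline requires both classes to be defined in advance. For the first class: "Anticipated adverse events for this study are defined as the adverse events listed in the questionnaire developed for this study", together with any other event reported in four cited studies. For the second: "Unanticipated adverse events will be defined as stroke, fracture, dislocation, or disc injury". No residual category is given.
- **Timing** (same section). "Participants will be asked to complete the questionnaire two days after each appointment as adverse events typically manifest within two days of chiropractic treatment". There are two appointments, at least one week apart (Abstract, Methods).
- **Form of the questionnaire** (same section). "We decided to use a questionnaire which consisted largely of predefined response options". It drew partly on open-ended questions in earlier studies. The form is an additional file that is not shown.
- **Two-week assessment** (4. Assessment at Two Week Follow-Up). The listed instruments cover pain, function, fear-avoidance, catastrophising, satisfaction, perceived change and blinding. None asks about adverse events.
- **Spontaneous route** (Withdrawing Participants from this Study). "If a participant reports to their chiropractor or research staff a severe adverse event they will be withdrawn from the study", with referral for medical care. On severity: "Any adverse event will be classified as severe if it is thought to be an emergency situation e.g. stroke", or if the associated pain is rated above 8 out of 10. No time limit is set on such a report.
- **Primary outcome** (Analysis of Adverse Events). Any adverse event, yes or no, compared between groups. Frequency and severity are reported descriptively.

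**The concern.** The first aim of this trial is the frequency and severity of harm, so the definitions and timing of harm collection matter more here than in most trials. Two things are fixed badly.

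First, a class meant for unforeseen harm contains only harms that the authors foresaw well enough to name. A new kind of event, found neither on the questionnaire nor in the four studies and not one of the four diagnoses, has no class to be reported under.

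Second, nobody is scheduled to ask about adverse events later than two days after a treatment, although every participant is assessed again at two weeks. What appears in between reaches the investigators only if the participant volunteers it, and the one route described for this covers severe events only. The text gives the consequences of such a report for the participant but not for the data. At stake is the completeness of the descriptive harms report, not the primary comparison.

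**Working it through.** **1. The plan's own figure.** The Sample Size section assumes 45% with an adverse event under usual care and 25% under sham, two-sided alpha 0.05 and 80% power, and states 90 per group. With pooled variance and no continuity correction:

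n = [1.96·√(2·0.35·0.65) + 0.8416·√(0.45·0.55 + 0.25·0.75)]² / (0.45 − 0.25)² = (1.322 + 0.555)² / 0.04 ≈ 88.1, so 89 per group.

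Power with 90 per group is 80.8%. The stated figure is reproduced. It rests on the any-event outcome, so this point does not touch it.

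**2. Are the two classes exhaustive?**

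| Event | Anticipated? | Unanticipated? | Can count as yes in the primary outcome? |
|---|---|---|---|
| On the questionnaire or in the four studies | yes | no, unless one of the four | yes |
| Stroke, fracture, dislocation, disc injury | only if also listed there | yes | yes |
| Anything else | no | no | yes, if reported |

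The third row is the gap. It is a gap in classification, not by itself a loss from the count.

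**3. How much time does scheduled collection cover?** Assume that each form covers the two days since the appointment; the form is not shown.

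- Between the two visits, which are at least 7 days apart: at most 2/7 = 29%.
- Whole period, if the second treatment is on day 7 and the two-week assessment is 14 days after it: (2 + 2)/(7 + 14) = 4/21 = 19%, with 14 − 2 = 12 days at the end without a scheduled question.
- Whole period, if the two weeks run from the first treatment instead: 4/14 = 29%, with 14 − 7 − 2 = 5 days at the end uncovered.

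The anchor of the two-week assessment is not stated. Treatment allocation offers the sham group usual care two weeks after the last sham treatment and once final outcomes are in. That fits the 19% case without settling it.

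**4. Does the spontaneous route fill the gap?** It is untimed, and its definition is open, with stroke only an example. But it covers severe events only, and the text does not say that a report made this way is recorded as a harms outcome. One of its two channels is the treating chiropractor. The Background gives chiropractors' involvement in data collection as a possible cause of underestimation in two earlier studies. Here the practitioners are unblinded (Blinding), and different practitioners treat each arm (Discussion).

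**The case against.** The strongest reply is that a missing label is not a missing event. A reader might infer that unlisted events go uncounted. The text does not support that: the primary outcome is not restricted by class, the questionnaire is only largely predefined, and an unlisted emergency falls under the open definition of a severe event. This part of the reply stands in full.

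A reader might also infer that usual care will look safer. The same definitions, form and timing apply in both arms. Bias would need late or novel events, or their reporting, to differ between arms, and the documents give no figure for that. Unblinded and different practitioners make differential reporting possible, but neither its presence nor its direction is shown.

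A third tempting step is to size the flaw by what 90 participants can exclude. With no events in 90, the one-sided 95% upper limit is 1 − 0.05^(1/90) = 3.3%. That is a limit of sample size and holds under any definition or window. For assumed true rates of 0.1%, 0.5%, 1% and 2%, the chance of at least one event in an arm, 1 − (1 − rate)^90, is 8.6%, 36%, 60% and 84%. Many rare events would go unseen even after the fix.

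Finally, the two-day window is a reasoned choice, justified by when events usually appear in earlier studies. That supports it for the primary endpoint. It does not explain why nothing is asked at a contact that takes place anyway. The Discussion does concede that probably only the most common events will be captured, but it attributes this to having two sessions, not to the definition or the window. The full protocol may say how spontaneous reports are recorded, so that part is a request to state it, not proof that it is absent.

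**Conclusion.** The point holds in a limited form. The unanticipated class is badly defined, because it cannot hold an unanticipated event. Scheduled collection ends two days after each treatment and covers an estimated 19% to 29% of the period up to the two-week assessment. That range depends on the unstated anchor, on a 7-day gap between treatments and on each form covering two days. Later non-severe events have no described route into the data. Later severe events have one, but the article does not say that they are counted.

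The effect is on the classification and completeness of the descriptive harms report. No effect on the primary comparison or on the sample size is shown, and neither loss of unlisted events nor bias towards usual care can be claimed. The change is still worth making, because harm is the first aim and the remedy is cheap.

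**What to change.** - **Definition.** In 3. Assessment of Adverse Event Events, define an unanticipated event as any adverse event not on the anticipated list. Keep the four diagnoses as named events of special interest, reported individually by arm.
- **Two-week assessment.** Add the existing adverse event questionnaire, with date of onset, to the two-week pack in both arms. Report events with onset after day 2 separately, as a secondary harms outcome.
- **Spontaneous reports.** State that every report made under Withdrawing Participants from this Study is recorded and counted in the harms analysis of the allocated arm, including reports from participants who are then withdrawn. This concerns recording only and leaves the withdrawal rule as it is.

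The cost is a few sentences and one more copy of an existing form at an existing contact. The downside is a longer recall period for the later events and slightly more burden on participants. The two-day primary endpoint, its analysis and the 90 per group stay as they are.
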